## Methods and analysis

### Design

The azithromycin to **‘**Prevent rEcurrenT Acute Lower Respiratory Infections’ (PETAL) trial is a parallel (1:1), double-blind, placebo-controlled, multicentre, international superiority RCT (figure 1). It aims to determine whether 6–12 months of azithromycin following ALRI hospitalisation reduces subsequent ALRIs and improves other clinical and economic outcomes. The first participant was randomised in October 2020, and we anticipate that recruitment will be completed by February 2025.

**Figure 1 F1:**
[figure not shown]
Trial design. ALRI, acute lower respiratory infection; NPS, nasopharyngeal swab; PC-QoL, parent-cough quality of life.

### Study settings and participants

#### Study sites

The RCT is being conducted in four hospitals across three countries: Australia, New Zealand and Timor-Leste. The Australian site is Royal Darwin Hospital (Darwin), the New Zealand sites are Starship Children’s Hospital (Auckland) and Kidz First Hospital (Auckland) and the Timor-Leste site is Guido Valadares National Hospital (Dili).

#### Inclusion criteria

(1) First Nations (Australian Aboriginal and/or Torres Strait Islander; or New Zealand Māori and/or Pacific Islander) or Timorese children aged <2 years; (2) hospitalised with an ALRI (bronchiolitis or pneumonia) and resident of the site hospitals catchment areas (in Darwin this includes two remote communities within the Northern Territory); and (3) requiring during their illness (including during hospital transfer or in the community) oxygen, respiratory or fluid (nasogastric or intravenous) support OR had an ALRI-related hospitalisation within the previous 3 months. In addition, New Zealand children are to be aged ≥3 months, a condition required by the local human research ethics committee (HREC).

#### Exclusion criteria

(1) Known chronic lung disease (eg, cystic fibrosis, radiographic-confirmed bronchiectasis, chronic neonatal lung disease); (2) receiving regular azithromycin (within the last 4 weeks); (3) macrolide contraindicated (eg, known liver dysfunction, hypersensitivity); (4) primary carer lacks a mobile phone and/or is unable to attend follow-up clinical visits over the next 24 months; or (5) participation in another respiratory-related RCT.

#### Recruitment

A good clinical practice (GCP)-trained researcher visits the paediatric wards of site hospitals daily (Monday to Friday) to identify potential participants. They approach the parents/guardian of the children fulfilling the eligibility criteria and explain the RCT, including its risks/benefits, using a plain language information booklet (flipchart-based). When required, interpreters are used. After the study is explained and the parents/guardian agrees to their child’s participation, written informed consent is requested from the parents/guardian (see online supplemental file). At enrolment, parents/guardian was also informed their child could opt out of taking the trial medication after 6 rather than 12 months. This was in response to some parents/guardians articulating concerns over the study duration. All participants are managed clinically according to standardised local protocols already in place at site hospitals.

#### Trial medications

Azithromycin provided as oral powder for suspension (200 mg/5 mL) is administered once per week for 6–12 months. Doses are weight based at 30 mg/kg/week. Equivalent placebo powder for suspension matches the active medication in taste and appearance. The Menzies School of Health Research (Menzies) purchased the trial medications (azithromycin and its corresponding placebo) from the Institute of Drug Technology (Melbourne, Australia), as done previously.^14 19 28^ Trial medications are shipped to sites by trial logistics companies.

#### Randomisation, allocation concealment and blinding

Randomisation is undertaken by each site’s pharmacy representative who allocates participants to a treatment according to a randomisation sequence. Each site has two randomisation sequences; one stratified by site and the other by whether the child has had a prior ALRI hospitalisation or not. An opaque envelope with the corresponding respective randomisation number is then opened to reveal treatment allocation as one of eight bottle letters (A–H), four allocated to azithromycin and four to placebo. The randomisation sequences were generated by an independent statistician using permuted blocks.

The first dose of trial medication is given in hospital and then dispensed weekly by either a member of the research team, primary health clinic staff or family member (whichever is appropriate) for each site. Adherence is monitored by the research team in weekly medication logs based on parent reports. People masked to the treatment allocation are those (1) receiving the treatment, (2) administering the treatment, (3) assessing the outcomes and (4) analysing the data.

#### Concomitant medications

If clinically indicated, participants may have non-macrolide antibiotics for respiratory or other infections while receiving trial medications. These data are captured on standardised data collection forms when undertaking medical chart reviews.

### Data collection, monitoring and follow-up details

Data are collected by GCP-trained researchers using standardised data collection forms similar to our previous RCTs.^14 15 28^ At enrolment, sociodemographic, clinical and economic data and nasopharyngeal swabs (where possible) are collected (table 1). Sociodemographic details include age, sex, anthropometrics, family and household size, exposure to tobacco smoking (mother and household), breastfeeding, immunisation history, medications (prior to and during hospitalisation), current and previous ALRI history, comorbidities and the eight-item parent-cough specific quality of life (PC-QoL) score.^29 30^ Clinical data include respiratory symptoms/signs, investigations and treatments before and during hospitalisation. These details are obtained either by the parent/guardians and/or review of the child’s medical records.

**Table 1 T1:** Schedule of visits and contact points

		Month					
	Baseline (hospital)	1	4	8*	12*	18	24
Screening for eligibility	√						
Written informed consent	√						
Randomisation	√						
First dose of study medication	√						
Medical history	√						
Medical chart review	√	√	√	√	√	√	√
Clinical assessment _(where possible)_	√	√	√	√	√	√	√
PC-QoL	√	√	√	√	√	√	√
NPS†	√				√	√	√
Semistructured interview							√

* Will instead be done at 6 months for children opting out of the intervention at the 6-month time-point.

† For children living in remote locations in the unlikely event where the research team are physically unable to visit and/or other avenues have been exhausted, specimen collection will not occur in these instances.

NPSnasopharyngeal swabPC-QoLparent-cough quality of life

Medication adherence and adverse events (diarrhoea, vomiting, rash, nausea) logs are maintained either by the parents/guardian or research staff during the intervention period.

Participants are followed up clinically, including obtaining PC-QoL scores, by the research team at 1, 4, 8, 12, 18 and 24 months. Participants, whose families opt out of taking the trial medication at 6 months because it was becoming a burden on family life, are clinically reviewed at 6 months rather than at 8 months. Participants will then either leave the study or remain within the study to be followed up until 24 months. Hospital and community medical charts (electronic and paper-based) will be reviewed at each visit for ALRIs and chronic respiratory symptoms/signs treated by the child’s local doctor that suggest underlying CSLD, while evidence of bronchiectasis at 24 months will be established by reviewing hospital records for chest HRCT scan and bronchoscopy results.

Where participants have moved communities or attended multiple primary healthcare facilities during their 24-month involvement with the study, we will use our established methods from previous RCTs (described above), where missing data were <10%.^14 19^

Exit criteria include consent withdrawn by the parents/guardian, and/or intolerance to trial medication determined by study site doctors or the independent data monitoring committee (iDMC). Unblinding if necessary, will be done by site pharmacy or independent representative.

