### Outcomes

The primary outcome is the annualised rate of medically attended ALRIs during the intervention period of 6–12 months when the participants received the trial medications. Outcomes are assessed at 6 and 12 months for those who received 6 and 12 months of study trial medication, respectively.

Secondary outcomes are the rates and proportions of children with:

ALRI hospitalisations during the intervention period at 6–12 months.ALRI hospitalisations during and post-intervention (at 24 months post-commencement of trial medications).Adverse events (eg, nausea, vomiting, diarrhoea and rash).Nasopharyngeal colonisation by macrolide-resistant respiratory pathogens at baseline, (6), 12, 18 and 24 months.Chronic respiratory symptoms/signs suggestive of underlying CSLD or bronchiectasis at 24 months.ICER on the potential benefits (in terms of savings in hospitalisations and medical evacuations, and other associated costs to health services and patients) of azithromycin compared with placebo over the additional costs of administering the drug.

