### Data monitoring, management and analyses

All study participants are assigned a unique study identifier at enrolment, which is the primary identifier on all study records including bio-specimen labels throughout the trial. Confidentiality is maintained in accordance with GCP guidelines and with respective HREC requirements at each site. All identifiable data from study participants are retained on a password-protected REDCap database and in locked filing cabinets at each study site. Each site is responsible for data entry. Data management is overseen by the principal investigator ([name]) at Menzies. Access to these data is only provided to immediate members of the research team except if requested by legislative or regulatory agencies, or by the respective HREC at each site.

All adverse and serious adverse events are monitored by an iDMC which was established prior to commencing the trial. Reference groups at each site oversee cultural aspects of the RCT.

A detailed statistical analysis plan will be prepared and approved by the chief investigators and the iDMC prior to undertaking the final analysis. Data will be audited, cleaned and locked before any analyses are undertaken. The investigators will only see analyses of pooled data until the statistical analysis code has been written (on pooled data) and agreed, and the trial has terminated. At this point, unblinding of investigators will occur. The analysis will be directed by a biostatistician. Results will be reported in accordance with the Consolidated Standards of Reporting Trials guidelines. We will use an ‘intention-to-treat’ approach for the primary analysis. Missing data will not be imputed. No interim analysis is planned. Any post hoc analysis or unplanned analyses will be described clearly.

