#### Primary aim

To determine the efficacy of azithromycin, the annualised rate of medically attended ALRIs in those randomised to receive 6–12 months of azithromycin will be compared with those receiving placebo (controls). A negative binomial regression model and incident rate ratio (IRR) 95% CI, including treatment group and the number of months taking treatment in the study included as an offset, will be used to determine between-group differences with 95% CIs. Subgroup analyses will be done for age (≤12, >12 months) and adherence (≤ or >70%).

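### Stopping trial medication is not separated from leaving follow-up, so children who stop for treatment-related reasons can be lost to the 24-month outcomes, with no imputation

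*Protocol article*

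**What the plan says.** All references are to the protocol article.

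- **Leaving.** The section on data collection, monitoring and follow-up reads: "Exit criteria include consent withdrawn by the parents/guardian, and/or intolerance to trial medication determined by study site doctors" (or by the data monitoring committee). For families who stop medication at 6 months because of its burden, the same section says: "Participants will then either leave the study or remain within the study to be followed up until 24 months".
- **Missing data.** The section on data monitoring, management and analyses promises an intention-to-treat approach for the primary analysis and then says: "Missing data will not be imputed".
- **Primary outcome.** Under Outcomes it is the "annualised rate of medically attended ALRIs during the intervention period of 6–12 months when the participants received the trial medications". Timing is also fixed there: "Outcomes are assessed at 6 and 12 months for those who received 6 and 12 months of study trial medication, respectively". Under Primary aim the model has "the number of months taking treatment in the study included as an offset".
- **24-month outcomes.** Under Outcomes and Secondary aims these include ALRI hospitalisations during and after the intervention, and "Chronic respiratory symptoms/signs suggestive of underlying CSLD or bronchiectasis at 24 months".
- **Source of outcome data.** The visit schedule (Table 1) has a medical chart review at every time-point. The follow-up section says that ALRIs, chronic symptoms or signs, and bronchiectasis are found from hospital and community records.

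**The concern.** Intolerance is a reason to stop a drug. Here it stands beside withdrawn consent as a reason to exit, in the section about follow-up, and no follow-up after such an exit is described. If exit means leaving the study, an event that can depend on the allocated treatment decides who supplies the 24-month outcomes. The comparison is then among children who tolerated the medication or chose to stay, and no imputation is allowed to address the gap. That sits badly with intention-to-treat.

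Nothing else in the article closes the gap. Replacing withdrawn or lost children (Sample size) restores numbers but says nothing about those who left. The tracing methods in the follow-up section are for children who moved or used several clinics. The loss is also largely avoidable, because the outcomes come from records and need neither a clinic visit nor continued medication.

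**Working it through.** **1. The plan's own attrition figure.** Inputs from Sample size: control rate 3 per child-year, IRR 0.6 (active rate 1.8), k = 0.4 taken as the dispersion, two-sided 5%, 90% power, 15% attrition. With one year of exposure:

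n = (1.960 + 1.282)² × [1/3 + 1/1.8 + 2(0.4)] / (ln 0.6)² = 10.507 × 1.689 / 0.261 = 68.0 per group

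68/0.85 = 80 per group, so the stated figure reproduces. The allowance is 80 × 0.15 = 12 children per arm.

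**2. What each route out costs, reading the text as written.**

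| Route | Primary rate as defined | 24-month outcomes |
|---|---|---|
| Stops at 6 months, stays | Assessed at 6 months | Observed |
| Stops at 6 months, leaves | Assessed at 6 months | Lost |
| Exits for intolerance | Events and months up to stopping count | Lost, if exit means leaving the study |
| Consent withdrawn | Events and months up to withdrawal count | Lost, unavoidably |

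So the loss falls on the right-hand column.

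**3. Worst-case bound for a 24-month proportion.** Let a share m be missing in each arm, RD_obs be the risk difference among observed children, and q_A and q_C be the unknown risks among the missing (azithromycin, placebo). Then

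RD_all = (1 − m) × RD_obs + m × (q_A − q_C), with q_A − q_C between −1 and +1.

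With RD_obs = 0 the range is ±m:

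| Share missing per arm | Source | Children of 80 | Bound (points) |
|---|---|---|---|
| 2% | 6-month opt-outs to date, if all left | 1.6 | ±2 |
| 10% | upper limit of missing data reported for earlier trials | 8 | ±10 |
| 15% | planned attrition | 12 | ±15 |

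The full width at 15% is 30 points; if only one arm loses children it is 15. The actual bias in one arm's proportion is m × (risk in leavers − risk in stayers). The article gives neither factor for intolerance exits, so this cannot be narrowed.

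**4. Effect of opt-outs on primary precision.** Information per arm is n × [(1 − s) × μ/(1 + kμ) + s × μt/(1 + kμt)], where μ is the yearly rate, s the share on 6 months and t = 0.5 year. With s = 2% and n = 68, this is 68 × (0.98 × 1.364 + 0.02 × 0.938) = 92.1 for placebo and 68 × (0.98 × 1.047 + 0.02 × 0.662) = 70.6 for azithromycin. Power is 89.8% against 90.0%, so this route costs almost nothing.

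**5. Why a 12-month sensitivity analysis is still useful.** Assume a share d of the azithromycin arm stops after s years, now the time of stopping, and returns to the control rate, with stopping unrelated to underlying ALRI risk. The on-medication IRR stays at 0.60. Over 12 months in all randomised children it is

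[(1 − d) × 1.8 + d × (1.8s + 3(1 − s))] / 3 = 0.60 + 0.40 × d × (1 − s)

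For s from 0.5 down to 0.1 year this gives 0.604–0.607 (d = 2%), 0.610–0.618 (5%), 0.620–0.636 (10%) and 0.630–0.654 (15%). These values of d and s are assumptions. The gap is a difference between two questions, on-medication rate and rate in all randomised children, and not an effect of non-imputation.

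**The case against.** The strongest reply is that exit is not defined. It could mean stopping medication only, and a condensed article may leave follow-up after stopping to the full protocol. For 6-month opt-outs, leaving is optional, only 2% had opted out, and azithromycin is described as well tolerated. A statistical analysis plan is still to come and can add sensitivity analyses. All of this stands, and it limits the point to wording that must be reconciled. It does not remove it: pairing intolerance with withdrawn consent points to leaving the study, and an analysis plan cannot recover records that were never collected.

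Three stronger readings are tempting but not supported:

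- **That the primary rate is biased by non-imputation.** As defined, a child who stops contributes the events and months up to stopping, and a 6-month opt-out has no missing primary outcome. The tension with intention-to-treat there comes from the on-medication window and offset.
- **That the 15-point figure dwarfs the effect of interest.** It treats all planned attrition as missing with extreme outcomes. Setting it against 8 to 10 points (40% of 19% or 25%) borrows the primary outcome's reduction and applies it to bronchiectasis at a median of 13 months and rehospitalisation at 6 months, neither of which is the 24-month endpoint. The 74% ongoing morbidity at 12 months, also in the Introduction, would give 0.74 × 40 = about 30 points.
- **That nothing planned would reveal the problem.** The article commits to CONSORT reporting and compares adverse events by arm, so unequal losses would probably be visible, though not corrected.

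**Conclusion.** The point holds in a limited form. The article does not separate stopping trial medication from leaving follow-up, and as written this allows treatment-related loss from the 24-month hospitalisation and CSLD/bronchiectasis outcomes, with imputation ruled out and intention-to-treat promised. It affects the 24-month proportions most. The hospitalisation rate suffers less if its model uses observed time. The effect on the primary outcome as defined is small.

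The size of any bias is unknown. The only firm figure is the bound of ±15 points, which assumes 12 of 80 missing in each arm, no difference among observed children and the most extreme outcomes in the missing. The conclusion rests on reading exit as leaving the study. If only medication was meant, the sentence still needs correcting. The change is worth making because it is cheap and the data source is already in place.

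**What to change.** Reconcile the follow-up, Outcomes, analysis and Primary aim sections as follows. None of this changes when medication is stopped.

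1. Record intolerance and 6-month opt-out as discontinuation of trial medication only. Chart-review follow-up continues to 12 and 24 months for every randomised child unless consent for record access is withdrawn.
2. Analyse the 24-month outcomes on all observed follow-up, by randomised arm.
3. For the 12-month ALRI rate, do the same at least as a sensitivity analysis, with observed follow-up time as the offset in place of months on treatment.
4. Replace the blanket rule against imputation with wording that allows a missing-data sensitivity analysis for the 24-month binary outcomes. The method, for example multiple imputation or a tipping-point analysis, can be left to the statistical analysis plan.

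The cost is an amendment, some extra chart reviews and added sensitivity analyses. The first child was randomised in October 2020, so children who have already left may not be recoverable without renewed consent. Recruitment was expected to end in February 2025, which puts the last 24-month follow-up at about February 2027, so the gain is greatest for children still in follow-up when the change is made.

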### Study definitions

#### ALRI

A medically attended episode of acute respiratory illness (ie, acute cough, dyspnoea, tachypnoea, new abnormal chest examination findings with or without fever or radiographic findings treated by primary healthcare or hospital staff). Clinic visits within 2 weeks of each other are considered part of the same ALRI.^19^

#### Bronchiectasis

Persistent or recurrent chronic (>4 weeks) wet or productive cough, often with other respiratory symptoms/signs (eg, breathlessness or auscultatory crackles), and frequent respiratory exacerbations (or ALRIs) with variable responses to antibiotics AND chest HRCT scan evidence of abnormally dilated bronchi.^27^ HRCT scans are not routine and only undertaken at the discretion of the attending physician.

#### CSLD

Chronic respiratory symptoms/signs of bronchiectasis but where either a chest HRCT scan has not been done or not shown radiographic evidence for this diagnosis.^19 31^

#### Treatment failure

If there are six community-treated ARLIs or three ALRI hospitalisations during the 12-month intervention (or prorata for those on 6 months). These are captured on the child’s electronic records as done previously.^19^ Where possible, participants will be offered a referral to either a paediatric respiratory specialist or paediatrician.

### Sample collection

Upper airway respiratory pathogen carriage and antibiotic resistance will be assessed using nasopharyngeal swabs in accordance with the WHO recommendations for pneumococcal carriage studies.^32^ At the end of the study, Australian and New Zealand samples will be tested at Menzies and Timorese samples tested at the Timor-Leste National laboratory using standardised culture protocols across all sites. Nasopharyngeal swabs will be thawed and cultured for *Streptococcus pneumoniae*, *H. influenzae*, *Moraxella catarrhalis* and *Staphylococcus aureus*. Antibiotic susceptibility of *S. pneumoniae*, *H. influenzae*, *M. catarrhalis* and *S. aureus* isolates will be determined by the European Committee on Antimicrobial Susceptibility Testing (EUCAST) disc diffusion method.^23^ The minimum inhibitory concentration for azithromycin will be determined by E-tests where non-susceptibility is identified by disc diffusion.^23^ EUCAST criteria will be used to define non-susceptibility, as done previously.^14 19 23^

### Future Microbiological studies

Microbiota analysis of nasopharyngeal swabs will be undertaken when funding becomes available. Where possible, oropharyngeal swabs and faecal samples (OMNIgene, DNA Genotek) for microbiota analyses will also be collected at baseline, 12 (or 6 months if opting out of trial medication at 6 months), 18 and 24 months and will be stored for future testing.

